## Exploratory endpoints

1. All-cause mortality one year after randomization
2. Difference in organ function, using the Acute Kidney Injury Network (AKIN) classification, liver function blood tests and others.
3. Incidence of all adverse events

# Study population

## Selection of participants and study setting:

The patient population is adult patients (18 to 80 years of age, as estimated by crew on-scene) that suffers from an out-of-hospital cardiac arrest with assumed non-traumatic origin, as determined by the physician on scene.

## Inclusion criteria

The subject must meet all the following criteria to be included in the trial:

- Estimated age between 18 to 80 years
- Out-of-hospital cardiac arrest
- Non-traumatic cardiac arrest
- Less than 10 minutes from debut of arrest to start of basic or advanced cardiac life support
- ACLS is established and can be continued

## Exclusion criteria

Fulfilling one criterion excludes the subject to be included in this trial.

- Traumatic cardiac arrest, including strangulation, electrocution and patients rescued from avalanches
- Accidental hypothermia with temperature < 32 ^0^C
- Suspected cerebral haemorrhage as aetiology of the arrest
- Suspected non-traumatic haemorrhage as aetiology of the arrest
- Pregnancy, obvious or suspected
- Patient included to the study site’s E-CPR protocol
- Other factors as decided by the treatment team (environmental factors, safety factors and others)

## Criteria for withdrawal or discontinuation

Patients can withdraw from the clinical study at any time without the need of a rationale and without compromise to their future medical care. If the patient has not regained ability to give consent, the next-of-kin can withdraw the patient from the study at any time. All patients will receive the same standard of care.

Any safety data on adverse events registered in patients that withdraw from the study will be stored in the database in an anonymized form, to ensure that no safety information is lost.

Patients that withdraw or are withdrawn from the study after randomisation will be replaced.

## Enrolment

Subjects with out-of-hospital cardiac arrest in the areas serviced by the study centres are candidates for enrolment into the study. Patients who develop cardiac arrest while being treated for other causes by ambulance personnel or the P-EMS crew are also eligible.

# Informed consent process

Because of the nature of the disease, patient in cardiac arrest cannot provide informed consent before randomisation and inclusion. Hence, the intervention will be performed before the patient or next-of-kin can provide informed consent or withdraw from the study.

According to regulations and as applied in on-going studies on cardiac arrest patients, the patient’s next-of-kin will be asked for an informed consent. During CPR an informed consent from the next-of-kin cannot be obtained, both due to that the crew are performing the CPR and because the next-of-kin is expected to be in a psychological state where it is not possible to process such information. The next-of-kin will therefore be asked for consent after the patients are admitted to the hospital or declared dead at scene. They will be contacted as soon as possible after the incident and all information will be given by a senior physician experienced in communication with next-of-kin to patients with critical illness. Patients regaining capacity to give an informed consent within 3 months will be asked for a deferred consent.

This process adheres to the ethical principles that have their origin in the Declaration of Helsinki. Prior to the start of this trial, the written informed consent form and any other information intended to be provided to the subjects has been approved by the regional ethical committee (REC).

The site investigator and/or designee (collectively named SI) will conduct the informed consent process of explaining the clinical study to the subject as well as providing the subject with a copy of the subject information sheet. The consent information will include all aspects of the clinical study that are relevant to the subject’s decision to participate in the language in which the subject is most proficient. The language will be non-technical and easily understood.

The SI will avoid coercion, will not appear to waive the subject’s legal rights in any way, will allow enough time for the subject to inquire about the details of the clinical study, ask any questions and make the decision to participate or not in the clinical study.

Should the subject decide to participate in the clinical study, the informed consent form will be signed and personally dated by the subject and the researcher who conducted the informed consent discussion. A copy will be given to the subject. Any significant relevant new information that arises during the clinical study will be provided to the subject and their consent to continue will be sought.

# Statistics

A separate detailed statistical analysis plan will be developed in cooperation with the study statisticians and will be published after approval from the steering committee, no later than before the first scheduled interim analysis.

A group sequential design with adaptive sample size modification is chosen to allow for the possibility of stopping the trial early due to significant differences in the primary endpoint or 30-day survival rate between the groups and to re-estimate sample size at the interim analyses to maintain the desired statistical power. This is described in chapter 9.3. Adaptive design has been advocated and used in clinical research due to several reasons ^40–43^. This includes cost-effectiveness regarding time and money, it might require fewer participants, ethical argument due to safety and efficacy of the trial intervention and that it might mimic the real-life medical practice more than a traditional randomized control trial.

## Statistical hypothesis

Null hypothesis H_0_: There is no difference in rate of return of spontaneous circulation between the control group (advanced cardiovascular life support only) and the intervention group (advanced cardiovascular life support + REBOA).

Alternative hypothesis H_A_: There is a difference in rate of return of spontaneous circulation between the control group (advanced cardiovascular life support only) and the intervention group (advanced cardiovascular life support + REBOA).

## Sample size

One prospective pilot feasibility study report that the procedure is feasible in the pre-hospital setting ^1^. This pilot study was without a control group, the number of patients was only 10, with 60 % rate of ROSC and with one survivor after 30 days. No other prospective studies are currently known to us. Therefore, we lack prospective data to allow a reasonable estimation of sample size for a conclusive trial design.

In Norway, the current overall rate of ROSC is 32% ^4^. Patient’s eligible for a REBOA procedure is however a cohort of this data material, which is defined by the inclusion and exclusion criteria, the duration of the dispatch and necessary procedure duration. The cohort is described in detail in a needs assessment for REBOA in non-traumatic OHCA in Norway and the reported rate of ROSC is markedly reduced to 18% ^33^.

The sample size needed to demonstrate a clinically relevant doubling of ROSC from 18% to 36%, with 0.80 power and a significance level of 0.05, is 94 patients in each group ^44^ (Figure 2).

[figure not shown]

*Figure 2. Estimated sample size with return of spontaneous circulation as primary endpoint. Horizontal line is drawn at the selected sample size n=100.*

We therefore choose to include 100 patients in each group.

## Interim analyses

Three interim analyses will be performed, after 30, 60 and 90 patients in both the intervention and the control group is included. No specific time schedule for interim analyses is set. The important variables to assess is the primary endpoint and 30-day survival with good neurologic outcome.

We will consider recommending the sponsor to stop the trial after interim analysis if there is a difference in primary endpoint or 30-day survival between the groups, with a significance level following the O´Brien-Fleming approach ^45,46^.

From the second interim analysis, we will perform a sample size calculation, based on the assumption that the current difference in primary endpoint between the two groups will persist. If the sample size needed to prove a difference is more than three times the planned sample size (with 0.80 power and a significance level of 0.05), we would consider recommending the sponsor to stop the trial due to futility.

On the last interim analysis, we will re-estimate the sample size in case of a non-significant difference on the primary endpoint. If the estimated sample size needed to prove a difference between the groups is above 100, but equal to or less than 150 in each group (with 0.80 power and a significance level of 0.05), the final sample size will be modified and we would recommend the sponsor to continue the trial until the modified sample size is reached.

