## The level of significance and power of the clinical study

It is not known if the REBOA can only be of benefit, it is also possible that it may decrease the chance of good outcome. Therefore, a two-sided test with significance level of 0.05 is chosen in the analyses. On the interim analysis, a significance level following the O´Brien-Fleming approach is chosen ^45,46^.

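### The sample-size extension at the third interim is unreachable at the protocol's own looks under an ordinary two-proportion test, and adds about 1 point of power or less in the other variants simulated, so it does not maintain power

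*Protocol*

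**What the plan says.** Chapter 9 (Statistics) describes a group sequential design with sample-size modification. One stated purpose is "to re-estimate sample size at the interim analyses to maintain the desired statistical power".

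Section 9.3 (Interim analyses) places looks at 30, 60 and 90 patients per group. From the second look, a size calculation is made on the assumption that the difference seen so far will continue. Stopping for futility is considered if the size needed exceeds three times the plan. At the last look, "we will re-estimate the sample size in case of a non-significant difference on the primary endpoint". The final size is then changed if the size needed, at 0.80 power and a 0.05 level, is "above 100, but equal to or less than 150 in each group".

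Section 9.6 sets the error levels: "a two-sided test with significance level of 0.05 is chosen in the analyses", and "On the interim analysis, a significance level following the O´Brien-Fleming approach is chosen". No boundary values or information fractions are given. Section 9.5 says only that dichotomous endpoints will be analysed by hypothesis testing.

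Section 9.2 gives the planning figure for ROSC of 18% v 36% ("with 0.80 power and a significance level of 0.05, is 94 patients in each group"), followed by "We therefore choose to include 100 patients in each group".

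**The concern.** The extension has two joint conditions, and both depend on the same observed difference at 90 per group. One asks that the difference be too small to cross the boundary. The other asks that it be large enough to give 80% power with no more than 150 per group. At 90% of the planned information the boundary is already close to the ordinary 0.05 level, so there may be no result that is small enough for the first condition and large enough for the second.

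At stake is a stated property of the design. The ethics committee, the funder and the data monitoring committee are told that the sample size adapts to preserve power. If the rule cannot be reached, or changes almost nothing when it is, that description is wrong. The results that more patients could help would get no extension.

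**Working it through.** **Inputs.** Two-sided level 0.05 (9.6); power 0.80, planned size 100 per group, rates 18% and 36% (9.2); looks at 30, 60 and 90 per group, non-significance condition and the 101 to 150 zone (9.3). Assumed: the observed difference drives the re-estimation, the final look is at 100 per group, and the test is the pooled two-proportion z (equivalently chi-square without correction).

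**1. The plan's own figure.** Pooled formula: n = [1.960·√(2p̄(1−p̄)) + 0.842·√(p₁(1−p₁)+p₂(1−p₂))]² / (p₁−p₂)². With p₁ = 0.18, p₂ = 0.36 and p̄ = 0.27 this gives 94.3 per group. The stated 94 is reproduced (95 if rounded up).

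**2. What needing N means at 90 per group.** To a close approximation z = (1.960 + 0.842)·√(90/N) = 2.80·√(90/N).
- N = 101: z = 2.64.
- N = 150: z = 2.17.

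**3. The third O'Brien-Fleming boundary.** For information fractions 0.3, 0.6, 0.9 and 1.0, by numerical integration:

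| Form | Third boundary | Two-sided p | N needed at that boundary |
| --- | --- | --- | --- |
| Classic | 2.157 | 0.031 | 90·(2.80/2.157)² ≈ 152 |
| Lan-DeMets | 2.113 to 2.121 | 0.034 to 0.035 | about 157 to 158 |

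The Lan-DeMets range reflects two ways of spending the two-sided level. If non-significant meant simply p > 0.05, N would have to exceed about 184.

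**4. Exact enumeration.** Over all pairs of event counts at 90 per group, 229 pairs need 101 to 150 by the pooled formula. Their z statistics run from 2.165 to 2.638 (p about 0.030 to 0.008). All lie above 2.157, so none is non-significant.

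**5. Examples near the planning rates.**
- 16/90 v 29/90: needs 140, z = 2.24, p = 0.025. Inside the zone but already significant.
- 16/90 v 28/90: needs 162, z = 2.08, p = 0.037. Not significant but over the cap.

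**6. Power (400,000 simulated trials per scenario, classic boundary).** Extensions: none. Power with and without the rule is identical: 0.818 (18% v 36%), 0.680 (18% v 33%) and 0.506 (18% v 30%).

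**7. Variants that the protocol leaves open, at the same three pairs of rates.**

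| Choice | Extension fires | Change in power |
| --- | --- | --- |
| Equally spaced four-look boundary (third value 2.338 classic, 2.298 Lan-DeMets) | 4 to 7% | +0.1 to +0.4 points |
| Lan-DeMets boundary scaled to 150 per group (2.554) | 14 to 16% | −0.2 to +0.3 points |
| Continuity-corrected test, three boundary sets | 4 to 14% | +0.6 to +1.0 points |

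With Fisher's exact test at the matched boundary, 22 of the 70 zone results with a lower count of 8 to 29 are non-significant (23 with the continuity correction). The first example above then has p = 0.038 (0.039 corrected), and the extension would fire. Power under Fisher's test was not simulated.

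**8. Who is left out.** The futility threshold is 3 × 100 = 300 per group, that is z = 2.80·√(90/300) = 1.53. Under the classic boundary, results with z from about 1.53 to 2.16 need about 152 to 300 per group. They are too small for the extension and too large for the futility rule.

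**The case against.** The strongest reply is that the protocol fixes neither the test nor the form of the boundary, and defers detail to a separate analysis plan due before the first interim. Those choices decide whether the rule is inert. This stands: that the extension never fires holds for an ordinary z or chi-square test with boundaries matched to the looks, and not universally. It does not rescue the power claim, because the zone and the non-significance condition are fixed in the protocol and power moved by about 1 point or less in every variant simulated.

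A second reply is that the assumption of a continuing difference appears in the futility paragraph. If re-estimation instead kept the planned doubling and updated only the control rate, control rates of 13 to 17% would give 145 to 103 per group whatever the interim p-value. The text does not exclude this, but it is the less natural reading: the extension, like the futility rule, turns on the size needed to prove a difference.

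Three stronger readings might be inferred, and the document supports none of them.
- *The design has no working adaptation.* The efficacy stop and the futility rule still function.
- *The rule would enlarge the trial to prove harm.* A result such as 16/90 control v 6/90 REBOA (p = 0.023, needed size about 135) is already significant at the matched boundary. It would trigger the extension only under a choice such as equal-look boundaries, which do not match the looks. Section 9.6 also chooses two-sided testing because harm is possible.
- *The trial's validity is threatened.* An extension that never fires adds no type I error and leaves power above the 0.80 target at the planning rates.

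**Conclusion.** The point holds in a conditional form. Given the observed difference as the basis, O'Brien-Fleming boundaries at 30, 60 and 90 of 100, and an ordinary two-proportion test, the two conditions for extension exclude each other and the probability of extending is zero. Under the other choices simulated it is roughly 4 to 16%, for a change in power of about 1 percentage point or less. Chapter 9 therefore claims a property that the rule does not provide. Power is about 0.82 at 18% v 36% because of the planned 100 per group, and it stays at about 0.68 and 0.51 at 18% v 33% and 18% v 30% under the matched classic boundary.

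Severity: should fix. The fault lies in a weak optional rule and the description attached to it; the primary comparison is not at risk.

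**What to change.** Before the first interim, delete the 101 to 150 extension from section 9.3 and the power-maintenance purpose from chapter 9. This is a wording change by amendment. It costs no patients and, on the matched reading, no power.

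If the sponsor wants to keep a re-estimation:
- name the test, the boundary form and the information fractions;
- redefine the trigger so that it can be reached under them, for example as a conditional-power zone within the existing cap of 150 per group;
- specify a final test that controls type I error after the change in size;
- restate what the rule adds to power.

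This alternative is a design choice, and its benefit is modest. One version, decided at 60 per group and in the direction of benefit only, would extend about 20% of trials and raise power at 18% v 36% from about 0.82 to 0.84 or 0.85. Either change should be made before unblinded data are seen, because a correction at the third look would be data-dependent.

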## Measures to minimize bias

**Selection bias**

This is a randomised study and randomisation happens on scene. This is important to minimise selection bias. Randomisation procedure is described in chapter 10.1.

**Performance bias**

The planned post-ROSC treatment, and treatment after admission to hospital, will not differ in the two groups. This is important to minimize performance bias. However, the intervention group will have the REBOA equipment in place when admitted and this will warrant specialized care and removal. It is also possible that the introducer sheath will be used for quick access to PCI or ECMO. We will gather in-hospital data to assess these eventual differences in in-hospital treatment.

**Exclusion bias**

The information regarding informed consent, follow-up of patient survival and other patient data, interview with performing personnel and procedure data is performed by a small number of personnel. Only one or two persons on each study site is responsible to collect this data. This same person is responsible for the registration of data to the CRF. This contributes to minimise exclusion bias.

**Detection bias**

The randomisation is blinded from the statisticians that perform the analyses. This contributes to reduce detection bias.

## Statistical design

The primary analysis will be according to intention-to-treat (ITT) principle, to compare the outcome between all participants randomised to the control group and the intervention (REBOA) group, i.e. all patients in the REBOA group will be included in the analysis regardless of actual occlusion of aorta. Per-protocol analyses will be considered if a considerable amount in the REBOA group has deviated from protocol and hence may undermine the validity of the ITT analysis. This deviation from protocol could result from that the patient either achieved ROSC or was declared dead before aortic occlusion, or the procedure was aborted of any reason.

The primary endpoint and other dichotomous secondary endpoints will be analysed using hypothesis testing. Continuous variables (end tidal CO2 values and blood pressure) will be analysed by regression methods.

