## The primary endpoint

The primary endpoint of this study is the proportion of patients that achieve return of spontaneous circulation (ROSC) with a duration of at least 20 minutes, i.e. sustained ROSC.

This clinical endpoint is based on the following Utstein definition updated in 2019 ^34^: *“Sustained ROSC is deemed to have occurred when chest compressions are not required for 20 consecutive minutes and signs of circulation persist.*”

Whether or not a patient has obtained ROSC is a comprehensive clinical assessment performed at regular intervals during the provision of CPR. This assessment is made in patients with an organized rhythm on ECG during pauses in chest compressions. ROSC should be suspected if one or more of the following occur ^34^:
•    Signs of life, including coughing, movement and/or regular breathing
•    Palpable pulses in radial, carotid and/or femoral arteries
•    Invasive systolic blood pressure > 50 mmHg

The current 2015 guidelines from the European Resuscitation Council state that a rise in measured end-tidal CO2 values (EtCO2) during CPR is indicative of ROSC ^10^. Establishment of REBOA may also give a transient increase in EtCO2 ^1^. There are no current cut-off values for EtCO2 deemed appropriate to use in this setting to indicate whether ROSC has occurred or not. Any rise in EtCO2 should be clinically assessed in conjunction with other signs of circulation.

If the patient has shorter periods of ROSC and do not obtain a persisting circulation, the patient has not met the primary endpoint. In the documentation, ‘any ROSC’, should be stated in these instances.

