## Specification of exploratory subgroups

This is the first large dataset to be collected on this intervention. Any subgroups that may have enhanced or reduced effect of the intervention is currently unknown. To assess the possible modifiers of the intervention effect, the following exploratory analyses will be used:

- Age
- Sex
- Type of initial rhythm (VF/VT or PEA/AS)
- Time from debut of arrest to aortic occlusion
- Study site
- Type of catheter used
- Hypoxemia as probable cause of arrest

These will be analysed using generalised linear models. This includes multiple regression analyses, which enable multiple imputation if necessary.

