### During Treatment

**Outline of a REBOA procedure at an out-of-hospital cardiac arrest**

The ambulance personnel and the P-EMS crew establish ACLS as per national guideline at site. Either manual compressions or a mechanical chest compression is used. Airway management is handled by either endotracheal intubation or a supraglottic airway device. Intravenous or intraosseous access on the upper body is established. Cerebral oximetry is used, if available. If the patient is eligible for inclusion, the patient is randomised by that the physician opens the next numbered sealed envelope from the REBOA equipment. The randomisation procedure is described in section 10.1.

The paramedic prepares the REBOA-equipment, while the physician prepares the ultrasound machine and examines the patient for visible femoral vessels. Most physicians are right-handed and therefore will prefer to cannulate the patient’s right femoral artery, while placed on the patient’s right side. The paramedic prepares the equipment at the patient’s foot. The femoral inguinal area is washed with antiseptic and a sterile drape covers the patient, from abdomen to distal.

Arterial cannulation is performed ultrasound guided, with out-of-plane technique (Figure 4).

[figure not shown]

*Figure 4. Ultrasound guided femoral arterial cannulation*

After the femoral artery and vein is identified, the artery is cannulated with a 19 G needle and a flexible guidewire is inserted 60 cm. The cannulation can be performed in the ventilation phase of CPR or a 10-20 second pause in chest compression is allowed for. This hands-off time is considered common practice. After the guidewire is placed, the needle is removed, and ultrasound images of the guidewire position is obtained and stored. A scalpel is used to make a small incision next to the guidewire, to widen the entrance point. A 7 Fr introducer sheath is inserted over the guidewire and the stylet is removed (Figure 5).

[figure not shown]

*Figure 5. Insertion of introducer in femoral artery*

If the catheter in use is the ER-REBOA catheter, the guidewire is also removed, and the balloon sheath is placed. If the catheter is the REBOA Medical balloon, the guidewire will remain and the catheter is placed over the guidewire, through the introducer. The balloon sheath is inserted 50 cm for a Zone 1 aortic occlusion (Figure 6) ^49^, by use of measure marks on the catheter. Zone 1 is favoured for best haemodynamic effect ^49,50^.

[figure not shown]

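### A per-protocol set that drops REBOA patients for ROSC or death before occlusion would be biased in either direction, and two listed effect modifiers cannot be estimated because controls have no value for them

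*Protocol*

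**What the plan says.** **Analysis sets (protocol 9.5).** The primary analysis is intention-to-treat: "all patients in the REBOA group will be included in the analysis regardless of actual occlusion of aorta". The section then adds: "Per-protocol analyses will be considered if a considerable amount in the REBOA group has deviated from protocol". It gives no threshold. It says such deviation could arise because "the patient either achieved ROSC or was declared dead before aortic occlusion, or the procedure was aborted of any reason". It states no corresponding rule for the control group.

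**Endpoint and timing.** The primary endpoint in 6.3 is "return of spontaneous circulation (ROSC) with a duration of at least 20 minutes, i.e. sustained ROSC". Under 11.1.2, "the patient is randomised by that the physician opens the next numbered sealed envelope from the REBOA equipment"; preparation, ultrasound, cannulation and inflation follow. All three causes of deviation therefore arise after randomisation.

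**Effect modifiers (protocol 9.8).** The list is introduced by: "To assess the possible modifiers of the intervention effect, the following exploratory analyses will be used". It includes "Time from debut of arrest to aortic occlusion" and "Type of catheter used", to be analysed with generalised linear models and, if needed, multiple imputation. Section 10.2.2 places the balloon catheter in the intervention group only. In the data tables of 12.2, the time of occlusion appears only among the additional items for the REBOA group.

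**The concern.** A patient who regains circulation before the balloon is inflated, or who is declared dead before then, has not departed from the plan. That is part of the course of the arrest, and controls have the same early events. If such patients leave the REBOA arm while their counterparts stay in the control arm, the arms are no longer comparable. Early ROSC lost from one arm lowers its success rate; early death lost from one arm raises it. The analysis would be called on when many patients were not occluded, which is when the selection is strongest.

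In 9.8 the difficulty is different. An effect modifier needs a value in both arms, and controls have neither an occlusion time nor a catheter. What remains is an association within the REBOA arm. For occlusion time that association is itself selected, because only patients still in arrest receive an occlusion time. A reader could take the result as evidence on how early occlusion must be achieved.

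**Working it through.** **1. The plan's own figure, for scale.** Section 9.2: ROSC 18% v 36%, power 0.80, two-sided 0.05, 94 per group. With pooled variance (mean rate 0.27):

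n = [1.96·√(2·0.27·0.73) + 0.842·√(0.18·0.82 + 0.36·0.64)]² / 0.18² ≈ 94.3

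This rounds up to 95, so the stated 94 reproduces within rounding. The planned effect is 18 points.

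**2. Per-protocol contrast with no true effect.** Let f be the share of an arm with ROSC before (would-be) occlusion and d the share declared dead before it. The protocol gives neither, so both are assumed. Early ROSC is counted as sustained. Assume 18% ROSC among patients who reach occlusion, and the same course in both arms.

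- REBOA after exclusion: 0.18
- Control, nobody excluded: f + (1 − f − d) × 0.18

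| f | d | Control | REBOA per-protocol | Difference (points) |
|---|---|---|---|---|
| 10% | 5% | 0.10 + 0.85 × 0.18 = 25.3% | 18% | −7.3 |
| 0 | 20% | 0.80 × 0.18 = 14.4% | 18% | +3.6 |
| 5% | 20% | 0.05 + 0.75 × 0.18 = 18.5% | 18% | −0.5 |

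**3. The same check with the control rate held at the planned 18%.** REBOA per-protocol rate = (0.18 − f)/(1 − f − d). Start from 100 per arm and remove exclusions from the REBOA arm only. Rejection rates come from exact enumeration of the two-sided pooled z-test.

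| f | d | REBOA per-protocol | Difference from 18% (points) | Rejection rate |
|---|---|---|---|---|
| 5% | 0 | 0.13/0.95 = 13.7% | −4.3 | 13.0% |
| 10% | 5% | 0.08/0.85 = 9.4% | −8.6 | 38.8% |
| 0 | 20% | 0.18/0.80 = 22.5% | +4.5 | 11.5% |
| 5% | 20% | 0.13/0.75 = 17.3% | −0.7 | 5.0% |

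Without exclusions (18% in both arms, 100 each) the rejection rate is 5.1%.

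**4. Estimability of the modifiers.** Write the model with columns 1, A (arm), X (modifier) and A·X. Controls have no X; give them any constant c. Then X = c·(1 − A) + A·X, a linear combination of the other three columns. The design matrix has rank 3 with 4 columns, for occlusion time and for catheter type alike. Main effect and interaction cannot be separated. Multiple imputation does not help, because the control values are undefined rather than missing.

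**5. Occlusion time within the REBOA arm.** An illustrative null simulation assumed, in minutes after randomisation, ROSC uniform over 0–40, death over 15–45 and scheduled occlusion over 5–25, with 18% ROSC whatever the scheduled time. Among patients actually occluded, ROSC fell from 15.1% (occlusion at 5–10 minutes) to 13.1%, 11.9% and 11.4% (20–25 minutes). The gradient is produced by selection alone. The times are assumptions.

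**The case against.** The strongest reply is that 9.5 does not define a per-protocol set. It says one may be considered, describes how deviations could arise, is silent on controls, and chapter 9 leaves detail to a separate statistical analysis plan. This limits the point: the protocol does not state that controls with early ROSC or death stay in. It does label these events as deviations, in the REBOA group alone, and says they may undermine the intention-to-treat analysis. A plan written from that text would inherit the problem.

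A reader might infer that exclusion is defined by the primary endpoint itself. The documents do not support that. Section 9.5 speaks of ROSC; 6.3 requires 20 minutes and says shorter ROSC does not count. The two are closely tied, not identical, and the arithmetic above counts every early ROSC as sustained.

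A reader might also infer that the per-protocol result would show spurious harm. That depends on f and d, which the protocol does not give; the sign can reverse or the bias nearly vanish. The 10% case is demanding: it puts 10/25.3, about 40%, of control ROSC before would-be occlusion.

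On 9.8, the analyses are exploratory and no interaction term is written out, so a REBOA-only description is possible. But the stated purpose is effect modification, which that description cannot deliver. Catheter type is also the weaker of the two items: under 10.2.2 it follows site practice, so its problem is estimability and confounding with site rather than selection on outcome.

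**Conclusion.** The point holds for supportive and exploratory analyses only. The intention-to-treat primary analysis, its error rate and the sample size are untouched.

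- **Per-protocol.** Dropping REBOA patients for ROSC or death before occlusion, with controls left whole, gives a biased contrast. In the assumed scenarios with no true effect, the error runs from −8.6 to +4.5 points against a planned effect of 18, and is close to zero when the two kinds of exclusion offset each other. No direction should be claimed.
- **Modifiers.** Neither time to occlusion nor catheter type can be assessed as a modifier of the treatment effect. This follows from the design and needs no assumed figure. Occlusion time within the REBOA arm is in addition selected on remaining in arrest.

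**What to change.** **In 9.5**, state that ROSC or death before occlusion is neither a protocol deviation nor a ground for exclusion, and that any restricted analysis applies the same restriction to both arms. An aborted procedure has no counterpart in controls, so it cannot serve as such a restriction.

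Two supportive analyses may be added, with their conditions stated:

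- A complier-average estimate (intention-to-treat difference divided by the share occluded). With no effect it returns zero; for example 0/0.85 when 15% are not occluded. It assumes that allocation acts only through occlusion. That is doubtful here, because 11.1.2 allows a compression pause for cannulation and 13.1.1 recognises a risk of interrupting ACLS. Its interval is wider than that of the intention-to-treat estimate.
- A landmark analysis in both arms, acceptable only if the landmark precedes occlusion. Otherwise it conditions on a status that occlusion may already have changed. It uses fewer patients.

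**In 9.8**, replace time to occlusion by time from arrest to randomisation as the effect modifier, and label occlusion-time and catheter-type analyses as descriptive within the REBOA arm. Catheter type stocked at the site at the date of randomisation may be used as a modifier instead, noting that it is largely confounded with study site, which is already on the list.

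**Cost.** Mainly wording, settled before the first interim analysis. Time of randomisation is listed in 12.2. Arrest time is already needed for the variable now in 9.8, but 12.2 has only a general entry for relevant times, so its capture should be confirmed. Stocked catheter type is not a listed data item for controls; the site catheter accounting in 10.2.3 may supply it. Time of ending resuscitation is not listed explicitly either and would be needed for a landmark analysis.
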